### Sample size

A sample size of 21 individuals on each group was the result of a calculation in which a level a significance (α) of 0.025 was adopted, with a power of 80%, a between-groups difference to be detected of 3.3 (SD = 3.1) days of headaches per month, and considering a loss of 20% at follow-up. The mean and standard deviation used in the sample size calculation were based on the reduction of the frequency of a gold standard pharmacologic treatment group for migraine management from a previous clinical trial [9]. For the primary outcome “headache intensity”, adopting the same parameters as the previous calculation, a sample size of 20 would be necessary to detect a between-groups difference of 1.52 (SD = 1.37) in the NPS, based on data from 4-week pharmacological treatment [53].

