**Methods:**

A two-armed, parallel-groups randomized controlled trial with 3 months of follow-up will be conducted. 42 individuals, both genders, aged between 18 and 55 years old with a medical diagnosis of migraine will be included. The intervention group will perform a protocol consisting of exercises for strengthening the muscles of the cervical spine. Participants within the sham ultrasound group will receive detuned ultrasound therapy in the upper trapezius muscle. Both groups will receive a weekly session for 8 weeks. The efficacy of each intervention will be measured by the frequency and intensity of migraine at a 3-months follow-up.

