**Conclusion:**

This study will aim to determine the efficacy of a neck-specific exercise program in reducing the frequency and intensity of migraine attacks. If the results show that a neck-specific exercise program is effective in reducing the frequency and intensity of migraine attacks, therapists will have a low cost and easily applicable tool to treat migraine.

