### Primary and secondary objectives

The primary objective of the current study is to determine the efficacy of a neck-specific strengthening exercise program in reducing the frequency and intensity of migraine attacks in subjects with migraine, compared with the sham ultrasound group. We also intend to determine whether craniocervical exercises influence the intensity of migraine attacks, migraine-related disability, concomitant neck pain, and the quantitative variables, including neck range of movement, pressure pain threshold, motor control of the deep flexor muscles, neck muscle strength, and resistance of cervical musculature.

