### Outcomes

The primary outcomes of this study will be the frequency and intensity of migraine. The frequency of headache attacks data will be collected by means of the headache diary, which will be delivered monthly to the patient. The frequency of migraine will be computed and analyzed in terms of days-of-pain per month. The migraine intensity will be also collected in the headache diary. The volunteers will classify the pain according to the numerical pain scale (NPS; 0–10) [32], and for the analysis of these data an average will be used. The secondary outcomes will be as follows: global perception of change, migraine-related disability, neck pain, cervical range of motion, pressure pain thresholds, muscle performance, observed by muscular strength, the cranio-cervical flexion test (CCFT), and the endurance of cervical musculature, in addition to the electromyographic parameters used in these tests.

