### Statistical analysis

All statistical analyses will be performed by a professional statistician and they will be blinded to the allocation groups. An intention-to-treat analysis will be performed in order to verify the effect on the outcomes. Intention-to-treat analysis is the most indicated statistical analysis method in randomized clinical trials because it allows verification of the real efficacy of the intervention, and avoids an overly optimistic estimate that may result from removal of the non-adherent volunteers [51]. Mixed linear regression models will be performed for the primary and secondary outcomes to estimate between-group and within-group comparisons. “Time” and “group” will be considered as fixed effects and participants as a random effect (random intercept model). Baseline will be used as a covariate and the term “interaction time by group” will be included in the model to evaluate the interaction effect of differences between groups at each follow-up and within-group differences over time. Additionally, post hoc Bonferroni correction will be performed for group comparisons at each follow-up in the case of a significant “time” X “group” interaction.

In addition, to determine the clinical relevance of between-groups differences, Minimal Clinically Important Difference (MCID) calculations will be performed for the variables that do not have the MCID described in the literature, and the Effect Size (ES) will be calculated based on the distribution methods. Differences will be considered clinically relevant when they overcome the MID combined with an ES > 0.4, following the criteria suggested by Armijo-Olivo et al. [52]

For the missing data, as recommended by CONSORT [29], imputation occurs through a mixed effect regression model*.*

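### The sample size powers each primary outcome as one comparison at 0.025, but the analysis section tests it through an interaction-gated Bonferroni over follow-ups, for which the stated 80% power was not calculated

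*Protocol article*

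**What the plan says.** **Outcomes.** The Outcomes section names two: "The primary outcomes of this study will be the frequency and intensity of migraine".

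**Sizing.** The Sample size section states that "a level a significance (α) of 0.025 was adopted, with a power of 80" per cent, and allows for a 20% loss. For frequency it takes a difference of 3.3 days per month (SD 3.1) and arrives at 21 per group. For intensity it keeps the same parameters, takes a difference of 1.52 (SD 1.37) on the 0–10 pain scale and arrives at 20. It gives no reason for 0.025 and makes no allowance for several time points.

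**Time points.** The Screening text under Study schedule places follow-ups at 1, 2 and 3 months after treatment ends. The Abstract (Methods) singles out the last: "The efficacy of each intervention will be measured by the frequency and intensity of migraine at a 3-months follow-up".

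**Analysis.** The Statistical analysis section fits a random-intercept mixed model with time, group, their interaction and baseline as covariate. Its only multiplicity rule is that "post hoc Bonferroni correction will be performed for group comparisons at each follow-up in the case of a significant" time-by-group interaction. It gives no significance level and no rule across the two primary outcomes.

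**The concern.** The two sections adjust in different dimensions. The sizing apparently divides alpha over outcomes and assumes one comparison per outcome. The analysis divides alpha over follow-ups, although the Abstract makes only one of them the measure of efficacy. The correction is therefore spent on months that are not the named endpoint, and its cost was never put into the sample size.

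The interaction gate adds a second mismatch. Baseline enters as a covariate. If the modelled times are therefore the follow-ups alone (an inference, since the article does not list them), the interaction asks whether the group difference changes between months. A benefit of 3.3 days that held steady from month 1 to month 3 would produce no interaction, and the follow-up comparisons might never be triggered. The sample size, by contrast, powers the difference itself.

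At stake is whether the trial has the power it claims for the comparison that decides it, and whether a reader can tell in advance which comparison that is.

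**Working it through.** **Inputs (Sample size section).** Frequency: difference 3.3, SD 3.1, so standardised effect 3.3/3.1 = 1.065. Intensity: 1.52/1.37 = 1.109. Alpha 0.025, power 80%, loss 20%, equal arms. Sidedness is not stated.

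**Step 1: reproduce the stated sizes.** Normal approximation, n per arm = 2(z₁₋α/₂ + z₀.₈₀)²/δ², with two-sided alpha 0.025:
- Frequency: 2(2.241 + 0.842)²/1.065² = 16.8, so 17. Then 17 × 1.2 = 20.4, so 21 as stated (17/0.8 = 21.25 would give 22).
- Intensity: 2(2.241 + 0.842)²/1.109² = 15.4, so 16. With loss, 20 by either inflation, as stated.

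One-sided 0.025, or two-sided 0.05, gives only 14 and 13 evaluable per arm (18 and 17 after dividing by 0.8). Two-sided 0.025 is therefore the level used, and 0.05/2 = 0.025 matches a split over two outcomes.

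**Step 2: completers.** 21 × 0.8 = 16.8, so 17 per arm.

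**Step 3: power at one follow-up under each rule.** Normal approximation: Φ(δ√(n/2) − z₁₋α/₂). For frequency, δ√(17/2) = 3.10. At 0.025/3 the critical value is 2.638, so Φ(3.10 − 2.638) = 67.9%. The noncentral t figure is given first in each cell and the normal approximation second.

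| Two-sided alpha | Frequency | Intensity |
|---|---|---|
| 0.025 (as sized) | 77.0% / 80.6% | 80.6% / 84.0% |
| 0.05/3 | 71.6% / 76.1% | 75.6% / 80.0% |
| 0.025/3 | 61.6% / 67.9% | 66.3% / 72.5% |

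The 77.0% in the first row reflects only the choice of t over normal approximation; it is not a multiplicity effect. On a like-for-like basis, the follow-up correction costs frequency about 13–15 points at 0.025/3 (80.6 − 67.9 = 12.7; 77.0 − 61.6 = 15.4) and about 5 points at 0.05/3 (80.6 − 76.1 = 4.5; 77.0 − 71.6 = 5.4) relative to the test that was sized.

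**Step 4: best case, no dropout (21 per arm).** Frequency: 74.5% / 79.1% at 0.025/3 and 82.4% / 85.4% at 0.05/3. Intensity: 78.8% / 83.1% and 85.8% / 88.5%.

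**Step 5: error rate over two independent outcomes.** At 0.025 each: 1 − 0.975² = 4.94%. At 0.05 each: 1 − 0.95² = 9.75%.

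**The case against.** The strongest reply is that this is a condensed article whose analysis plan is not shown. The per-test level may be stated there, and its absence here is no fault. The value 0.025 is exactly what a split over two primary outcomes requires. That stands, and it rules out several stronger readings that a reader might infer:

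- **That the familywise error is inflated.** The 9.75% arises only if each outcome is tested at 0.05, which the article nowhere says. At 0.025 each, error is controlled.
- **That error control and power both fail.** They fail together only with 0.05 per outcome plus the follow-up correction. Even then intensity power is 80.0% by the normal approximation. At 0.025 on the 3-month contrast alone, error control holds and power is about as planned.
- **That any outcome or month can be picked.** A gated Bonferroni over follow-ups guards against picking a month.
- **That both outcomes must succeed.** The Abstract's phrase "effective in reducing the frequency and intensity of migraine attacks" looks ahead to possible results and is not a success criterion.
- **That intensity's status is in doubt.** The objectives name it as primary and then add: "We also intend to determine whether craniocervical exercises influence the intensity of migraine attacks". The repetition is an editorial slip, because the Outcomes and Sample size sections both treat intensity as primary.

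It is also fair that the power figures use a plain two-sample comparison of completers, while the plan is an intention-to-treat, baseline-adjusted mixed model. At 0.025/3, frequency needs 22 (normal) to 24 (t) evaluable per arm for 80%. Adjustment would restore this if it cut the residual variance to 17/22 = 0.77 or 17/24 = 0.71, roughly a quarter less. The article gives no baseline correlation and takes its SD from a reduction in frequency, so the actual gain cannot be computed.

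None of this removes the mismatch. The article states both rules, and they differ.

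**Conclusion.** The point holds as an inconsistency between the Sample size and Statistical analysis sections. The stated 80% belongs to a single comparison per outcome at two-sided 0.025. Under the stated rule, with three follow-ups and 17 completers per arm, frequency power is about 62–68% (base alpha 0.025) or 72–76% (base alpha 0.05). Intensity power is about 66–73% or 76–80%. Frequency falls short on either base alpha.

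These figures assume a two-sided test, Bonferroni over the three listed follow-ups, the full 20% loss and no gain from baseline adjustment. They leave out any further loss from the interaction gate, which the article gives no means to compute. A fourth comparison would lower the figures further, but the article lists only three follow-ups. Loss of error control is not shown.

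**What to change.** In the Statistical analysis section, state that:
- the primary contrast for each primary outcome is the baseline-adjusted group difference at the 3-month follow-up;
- it is tested at two-sided 0.025 per outcome, whether or not the interaction is significant and without the follow-up Bonferroni;
- the 1- and 2-month comparisons are secondary;
- conclusions are reported outcome by outcome.

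In the Sample size section, say that 0.025 is 0.05 divided over the two primary outcomes, if that was the intention.

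This takes a few lines and adds no participants. The price is that the earlier follow-ups lose confirmatory status.

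If the follow-up correction is kept for the primary test instead, restate the power. At 0.025/3, 80% power for frequency needs 22 evaluable per arm by the normal approximation (22/0.8 = 27.5, so 28 recruited) or 24 by the t distribution (24/0.8 = 30), against the planned 21 recruited per arm.

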### Participants

Volunteers for the study will be included if they are between 18 and 55 years old, are of either sex, have been diagnosed with migraine according to the third edition of the International Classification of Headache [3], and have exhibited at least 3 days with migraine attacks in the previous month [31]. The inclusion and exclusion criteria are fully described in Table 1.

**Table 1 Tab1:** Inclusion and exclusion criteria

Inclusion	Exclusion
18–55 years old	Another type of headache
Both sexes	Medication overuse headache
Diagnosis of migraine	History of trauma in the cervical and/or face
Minimum of 3 days with migraine/month	Diagnosis of hernia or disk degeneration in the cervical region
	Systemic diseases^a^
	Pregnancy
	Anesthetic block in the three months prior to the selection process
	Have received manual techniques or therapeutic exercises in the last year in craniocervical region

^a^e.g.: fibromyalgia, diabetes, peripheral neuropathies

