### Interventions

This study will be performed to compare a neck-strengthening exercise protocol with a sham ultrasound group in migraine subjects. In both groups, there will be a combination of home stretching exercises. The interventions in both groups will last for 2 months. After completion of treatment, patients of both groups will be followed up by phone at 1, 2, and 3 months.

Intervention group (IG): the 8-week exercise program to be used in this study will be based on the protocol described by Falla et al. [28], which consists of specific exercises to strengthen the flexor and extensors muscles of the neck. Participants will receive instructions and guidance from a trained therapist for 30 min once a week. The protocol consists of two stages:
*Stage 1:* The first stage, of 6-week duration, will focus on incremental craniocervical flexion in a relaxed, supine position and craniocervical extension, flexion, and rotation in a prone-on-elbows position while maintaining the cervical spine in a neutral position (Fig. 2) [28]. The initial proposal for the deep flexors and extensors of the cervical spine will be 2 sets of 10 repetitions. However, for the deep flexor muscles, the movement should be initially sustained for 10 s. If the participant cannot perform the targeted program, the number of sets, repetitions, and time of sustentation (for the deep flexors) will be redefined. According to the tolerance of the patient, the sets, repetitions, and time of sustentation will be increased weekly [28].*Stage 2:* The second stage, of 2-week duration, consists of both flexor and extensor exercises with higher load, using head weight as the load [28]. A neck flexion associated with a head flexion will be performed with the participant in the supine position, removing the head from the stretcher. For the extension exercise, while performing the neck extension the patient will be instructed to maintain the cervical spine in the neutral position, and the body in the position of 4 supports (Fig. 3). Each of the exercises will be for 3 sets of 15 repetitions at a time over the course of 2 weeks [28].

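### The 3.3-day between-group target behind the 80% power is, by the protocol's own account, a reduction within one drug-treated group, so its source does not support it as an exercise-versus-sham difference

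*Protocol article*

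**What the plan says.** The Sample size section derives 21 participants per group. The stated inputs are alpha ("a level a significance (α) of 0.025 was adopted"), power of 80%, a 20% loss at follow-up, and "a between-groups difference to be detected of 3.3 (SD = 3.1) days of headaches per month". The next sentence gives the origin of that mean and SD: they were "based on the reduction of the frequency of a gold standard pharmacologic treatment group for migraine management from a previous clinical trial".

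For the second primary outcome, the section reports that 20 would be needed for "a between-groups difference of 1.52 (SD = 1.37) in the NPS, based on data from 4-week pharmacological treatment".

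The contrast under test is strengthening exercise against sham ultrasound, and the Interventions section adds: "In both groups, there will be a combination of home stretching exercises". The sham arm also has a weekly session for 8 weeks.

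Strengths and weaknesses of the study lists as a limitation that the mean and SD used for the sample size came from another study population. It says nothing about the type of contrast they represent.

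**The concern.** Two adjacent sentences describe the same number differently. One calls 3.3 days a difference between groups; the other traces it to the reduction seen in a single drug group. A one-arm reduction contains natural course, regression to the mean and placebo response as well as any treatment effect. A comparator with home stretching, weekly contact and a sham device can be expected to share some of that. The protocol itself, under Strengths and weaknesses, anticipates that sham participants may feel well attended to and perceive improvement.

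If the comparator improves by c days and the exercise arm matches the drug arm, the difference to be detected is 3.3 − c, not 3.3. The Sample size section then gives a reader too favourable a picture of what 42 participants can detect on a primary outcome.

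**Working it through.** **Inputs.** From Sample size: alpha 0.025, power 80%, difference 3.3 with SD 3.1 (frequency), difference 1.52 with SD 1.37 (intensity), loss 20%, 21 per group. Sidedness is not stated; the published numbers reproduce with a two-sided test.

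**1. Reproducing the plan's figures** (two-sample normal approximation)

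n per arm = 2 × [(z₁₋α/₂ + z₁₋β) × SD / difference]², with z values 2.2414 and 0.8416, sum 3.0830.

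- Frequency: 2 × (3.0830 × 3.1 / 3.3)² = 16.78; divided by 0.8 = 20.97, giving 21.
- Intensity: 2 × (3.0830 × 1.37 / 1.52)² = 15.44; divided by 0.8 = 19.3, giving 20.

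Both match, so the calculation is sound. The question concerns the input.

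**2. Power at the stated target**

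21 less 20% is 16.8, taken as 17 completers per arm. At a true difference of 3.3 days, power is 81% by the normal approximation. By the t-test (noncentral t, 32 df, noncentrality 3.3/3.1 × √(17/2) = 3.10) it is 77%. The unadjusted t-test reaches 80% at about 3.4 days.

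**3. Power if the comparator improves**

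The comparator improvement c is an assumption; the document gives no value. The exercise arm is held at a 3.3-day reduction, so the true difference is 3.3 − c. SD 3.1, 17 per arm, two-sided 0.025.

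| Assumed c (days) | True difference | Unadjusted t-test | Baseline-adjusted, correlation 0.5 | Baseline-adjusted, correlation 0.7 |
|---|---|---|---|---|
| 0 | 3.3 | 77% | 88% | 84% |
| 0.5 | 2.8 | 61% | 75% | 69% |
| 1.0 | 2.3 | 44% | 56% | 50% |
| 1.65 | 1.65 | 23% | 30% | 27% |

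The adjusted columns are there because the Statistical analysis section plans a model with baseline as covariate. They assume that 3.1 is the SD of a change score and that variances are equal at baseline and follow-up. Adjusting for baseline then multiplies the variance by (1 + r)/2, which is 0.75 at r = 0.5 and 0.85 at r = 0.7. The correlations are assumptions too.

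**4. Intensity**

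With 17 per arm and SD 1.37, the t-test has 81% power at 1.52 points. No reduced-difference calculation is pressed here, because the text does not say whether 1.52 is a within-group change.

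**The case against.** The strongest reply is that power is always conditional on a target. The section states its target, SD, alpha, power and loss, and at that target the number is correct. That stands. A reader might infer that the design simply lacks its stated power; the documents do not support that, because no true exercise-versus-sham difference is known. What fails is the stated basis for 3.3 days. The section does not defend it as a chosen minimal important difference; it gives the drug-group reduction as its source.

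Second, the planned baseline-adjusted model may be more precise than a t-test. This also stands, and it rules out claiming that 80% power is available only from 3.4 days upward. At correlation 0.5 the corresponding difference is about 3.0 days (3.41 × √0.75 = 2.96). Extra precision still does not turn a within-arm change into a between-arm effect, and the decline down the table remains.

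Third, the borrowing is partly disclosed. But a different population is not a different type of contrast, and a reader of that limitation would still take 3.3 to be an observed between-group difference.

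Two further readings are tempting and should not be pressed:

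- That the intensity target has the same fault. The text says only "based on data from 4-week pharmacological treatment", without mention of a single arm or a change from baseline.
- That 3.3 days is impossible given the entry criterion "Minimum of 3 days with migraine/month". Three days is a floor for individuals, not the expected mean; no baseline mean is given, and the floor does not bound a difference in group means.

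Nor does the protocol say that a non-significant result would be read as proof of no effect. An optimistic target does not bias the estimate or inflate the type I error.

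**Conclusion.** The point holds for frequency. The figure that sets the sample size is presented as a between-group difference while its stated source is a reduction within one drug-treated group. The two descriptions agree only with a comparator that does not change, which is hard to expect of an arm with stretching, weekly contact and a sham device. The 80% is valid conditionally, on a difference its source does not support.

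The size of the problem depends on the unknown comparator improvement. If the sham arm achieves half the drug-group reduction, power is about 23% unadjusted and about 30% with baseline adjustment at correlation 0.5. If it improves by half a day, the figures are 61% and 75%. These rest on SD 3.1, 17 completers per arm, two-sided alpha 0.025 and an exercise effect equal to the drug-arm reduction. For intensity, the type of contrast is an open question to be settled from the source.

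**What to change.** In the Sample size section:

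1. Describe 3.3 (SD 3.1) days as the within-group reduction in a drug-treated arm of another trial, not as an expected between-group difference.
2. State that 80% power holds only if the true between-group difference is about that large: roughly 3.3 to 3.4 days without baseline adjustment.
3. Give power for a range of smaller differences, naming the assumed SD, the number analysed and the analysis model, including the baseline correlation if adjustment is assumed.
4. Check in the cited source whether 1.52 (SD 1.37) is a within-group change or a between-group difference, and relabel it only if it is the former.

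N need not change. The cost is rewording one paragraph, one check of a reference, and a less favourable power statement.
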